### Exploratory Analyses

To assess feasibility and acceptability, we will report the drop-out rate and descriptive data on acceptability and feasibility. Using structural equation modelling that will allow us to model change over time, we will explore whether reward anticipation and motivation mediate the relation between treatment and behavioral activation and treatment and depressive outcome, respectively. Baseline scores on everyday mental imagery use, symptoms of anhedonia, avoidance tendencies, and the ability to generate reward imagery will be tested as potential moderators of the effect of treatment on outcomes (behavioral activation, depressive symptoms).

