#### Measurements

Participants complete questionnaires at baseline, Weeks 1-3, and follow-up (Week 5; see Table 1 for a complete list of measures, forms, and sampling points) as part of the respective online sessions. Session invitations will be sent out via email. If participants fail to respond to a given session invitation by accessing the provided link within 24 hours, a reminder message is sent out. The link in the reminder message is valid for another five days; if this period elapses without response, the respective participant is excluded from further participation in the study.

**Table 1 t1:** Measures and Sampling Points

Measure	Screening	Session 1/ Baseline	Session 2	Session 3	Session 4	Follow-up
Primary outcomes						
BADS		x	x	x	x	x
BDI-II	x	x			x	x
Secondary outcomes						
Items on acceptability and feasibility						x
WEMWBS		x			x	x
Activity data						
Activity monitoring form		x		x	x	
Activity ratings			x	x		
Potential mediators (measured as activity ratings)						
Reward anticipation			x	x		
Motivation			x	x		
Potential moderators						
CBAS		x	x	x	x	
FRIS		x			x	
SUIS		x				
TEPS		x				

*Note.* BADS = Behavioral Activation for Depression Scale (Kanter et al., 2007); BDI-II = Beck Depression Inventory-II (Beck et al., 1996); CBAS = Cognitive Behavioral Avoidance Scale (Ottenbreit & Dobson, 2004); FRIS = Freiburg Reward Imagery Scale (https://osf.io/9y64q); SUIS = Spontaneous Use of Imagery Scale (Kosslyn et al., 1998); TEPS = Temporal Experience of Pleasure Scale (Gard et al., 2006); WEMWBS = Warwick-Edinburgh Mental Wellbeing Scales (Tennant et al., 2007).

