#### Wait-List Control Condition

For participants in the wait-list control condition, the number and frequency of sessions is identical to those of participants in the Imagery BA condition. However, session contents are restricted to the collection of questionnaire data only. Participants in the wait-list control condition can choose to complete the Imagery BA intervention starting one day after the follow-up assessment.

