#### Activity Data

##### Activity Ratings

To assess individual differences and changes in reward anticipation and motivation, participants in the Imagery BA condition will be asked to provide ratings of the following items pre and post intervention, that is, before and after the imagery-enhanced activity scheduling procedure: (a) how pleasant they expect the activity to be, (b) how rewarding they expect the activity to be, and (c) how motivated they are to engage in the activity. To control for potential differences in activity characteristics, ratings of activity importance, procrastination tendency, and previous engagement with the activity will be obtained pre intervention. As a manipulation check, allowing to infer whether participants succeeded in generating mental imagery, participants in the Imagery BA condition will rate mental imagery vividness and anticipatory pleasure (i.e., pleasure experienced while imagining the activity) post intervention.

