##### The Ability to Generate Reward Imagery

The ability to generate reward imagery will be measured at baseline and Session 4 using the Freiburg Reward Imagery Scale (FRIS), a newly developed scale assessing individual differences in the ability to generate mental imagery of future activities including the associated positive emotional outcomes (for details, see pre-registration at https://osf.io/9y64q). For this scale, respondents are instructed to imagine engaging in a rewarding activity and subsequently rate the resulting mental image (subscales include vividness, anticipatory pleasure, anticipated pleasure, and motivation). Respondents rate their agreement with 12 statements (e.g., “This activity would make me happy.”) on an eleven-point scale ranging from 0 “not at all” to 10 “completely”.

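### The planned mediation of the treatment effect by reward anticipation and motivation cannot be estimated, because both are rated only in the Imagery BA arm

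*Protocol article*

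**What the plan says.** The Exploratory Analyses section plans a structural equation model in which "we will explore whether reward anticipation and motivation mediate the relation between treatment and behavioral activation and treatment and depressive outcome, respectively". Treatment is the exposure, so the quantity sought is the indirect effect of randomised arm through each mediator. The closing word of the quote leaves open which mediator goes with which outcome, but the point is the same under either reading.

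Four other places settle what data the model would have:

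- Table 1 (Measurements) lists reward anticipation and motivation under "Potential mediators (measured as activity ratings") and marks them at Sessions 2 and 3 only.
- Activity Ratings says that "participants in the Imagery BA condition will be asked to provide ratings of the following items pre and post intervention", and explains the timing as "before and after the imagery-enhanced activity scheduling procedure".
- Wait-List Control Condition says that for this arm "session contents are restricted to the collection of questionnaire data only", and that its participants "can choose to complete the Imagery BA intervention starting one day after the follow-up assessment".
- The Ability to Generate Reward Imagery describes a related questionnaire whose "subscales include vividness, anticipatory pleasure, anticipated pleasure, and motivation". This ability "will be measured at baseline and Session 4 using the Freiburg Reward Imagery Scale (FRIS"). Table 1 lists the scale as a potential moderator, and the article does not link it to the mediation model.

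**The concern.** Mediation of a treatment effect has two parts: the effect of treatment on the mediator, and the effect of the mediator on the outcome given treatment. The first is a contrast between arms. If the mediator exists in one arm only, that contrast has no data.

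The introduction presents the link from procedure through candidate mechanisms to outcome as something the study will illuminate, and names reward anticipation, motivation and behavioral activation as the candidates. For the first two, the analysis as written cannot deliver an indirect effect. A wording that promises one invites readers to treat whatever is estimated from the ratings as evidence of mediation.

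**Working it through.** The plan states no figure for this analysis, so there is nothing to reproduce. The check is one of identifiability.

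**Step 1. Who has mediator data.** Ratings are given around imagery-enhanced scheduling (Activity Ratings). Wait-list sessions contain questionnaires only, and that arm can start the intervention only after follow-up, which is after the last outcome measurement (Wait-List Control Condition). Control participants have therefore scheduled no activity to rate, and ratings they give later cannot serve. With recruitment of 192 in two equal arms, 192/2 = 96 controls would have 0 mediator values. Among 140 complete datasets the figure is 0 of about 140/2 = 70, if completion is equal in both arms.

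**Step 2. The mediator equation.** Write M = i + a·T + error, with T = 1 for Imagery BA and 0 for wait-list. In the full sample the design matrix (intercept, T) has rank 2. In the rows where M is observed, T = 1 throughout, the two columns are identical, and the rank is 1. Only the sum i + a, the Imagery BA mean, can be estimated. The path a is not identified, and so neither is the indirect effect a·b. The direct effect then cannot be separated from the total effect. A larger sample changes none of this.

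**Step 3. How far the answer is left open.** As an illustration with assumed values (simulated data, 70 per arm, mediator with unit residual SD), the observed data were held fixed and only the unobserved control mean of M was varied. The observed Imagery BA mean was 0.41, so a = 0.41 − (control mean). The indirect effect is a times the within-arm slope, and the direct effect is the total minus the indirect.

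| Assumed control mean of M | a | Indirect effect | Direct effect |
|---|---|---|---|
| −1 | 1.41 | 0.66 | −0.42 |
| −0.5 | 0.91 | 0.43 | −0.18 |
| 0 | 0.41 | 0.19 | 0.05 |
| 0.5 | −0.09 | −0.04 | 0.28 |
| 1 | −0.59 | −0.28 | 0.52 |

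Indirect and direct effects sum to about 0.24 in every row. The same data fit an indirect effect of either sign. The numbers only show that the result is set by the assumption; they are not a forecast for this trial.

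**Step 4. What can be estimated.** The association between ratings (or their change from before to after imagery) and later BADS or BDI-II within the Imagery BA arm can be estimated. So can a path from treatment through BADS to BDI-II, because Hypotheses 1 and 2 compare both scales between the arms, with BADS at five time points and BDI-II at three.

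**The case against.** **Table 1 is not split by arm, and no sentence expressly bars wait-list participants from rating activities.** This is correct, and the zero count is an inference, not a figure in the article. The inference is strong: the ratings are assigned to one named arm, tied to a procedure the other arm does not undergo, and no section gives the control arm a rating.

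**Structural equation modelling can handle missing data, or the before-and-after ratings can supply the contrast.** Full-information likelihood or imputation does not help when a variable is absent by design for a whole arm; its control mean would rest entirely on untestable assumptions. The before-and-after change also exists in one arm only, and BADS and BDI-II are not measured around each imagery task.

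**The pre-registration or a fuller plan may give the model.** It may describe a within-arm model, which would be sound under another name. It cannot create control-arm ratings. The conflict lies between things the article does state: the exposure, the measure and who is measured.

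**The analysis is exploratory.** This stands and limits the weight of the point. Exploratory status excuses low power, but not a parameter that cannot be estimated.

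Three stronger readings are tempting, and the article supports none of them. A reader might infer that the whole mechanism question fails. It does not: behavioral activation, which the Discussion treats as the putative mechanism, is measured in both arms. A reader might infer that the main results are compromised. They do not depend on this analysis. A reader might infer that the authors will report a within-arm correlation as mediation. That is a guess about conduct with no textual basis.

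**Conclusion.** The point holds for reward anticipation and motivation as the article defines them. With no control-arm values, the treatment-to-mediator path and the indirect effect are not identified at any sample size. This rests on reading Table 1, Activity Ratings and Wait-List Control Condition together as leaving the ratings to the Imagery BA arm.

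It should be fixed, but it does not threaten the trial. It concerns two of the three named mechanisms in an exploratory analysis. The two hypotheses, the primary BADS and BDI-II comparisons and the sample size are untouched.

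**What to change.** **Main change, in Exploratory Analyses.** Describe the activity-rating analysis as a process analysis within the Imagery BA arm, in which change in ratings from before to after imagery at Sessions 2 and 3 predicts later BADS and BDI-II. Do not call it mediation.

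**For mediation of the randomised effect,** use a measure taken in both arms. The natural choice is BADS at Sessions 2-4 as mediator of follow-up BDI-II, the mechanism the Discussion already describes. It needs no new data. As in any mediation analysis, randomisation does not protect the mediator-to-outcome path, so the no-confounding assumption should be stated.

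**Optional addition.** The FRIS anticipatory-pleasure, anticipated-pleasure and motivation subscales at Session 4, adjusted for baseline, could be mediators of follow-up outcomes only. FRIS is part of the questionnaire set, and nothing restricts it to one arm. Its limits should be stated:

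- It is designated a moderator reflecting imagery ability.
- Its one post-baseline wave coincides with the Session 4 outcomes, so it cannot address mediation of the end-of-treatment effect.
- It concerns a generic imagined activity, not the participant's own scheduled ones.
- Only the Imagery BA arm receives imagery training before the end of follow-up, so a between-arm difference may reflect trained skill and not reward anticipation or motivation.

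**Cost.** The cost is wording only, with no added data collection and no change to what either arm does. What is given up is the claim that reward anticipation and motivation, measured as activity ratings, mediate the treatment effect. Collecting such ratings from wait-list participants would be the alternative, but it would change the content of that arm.

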## Discussion

We presented a study protocol of a randomized controlled trial testing the effects of an online-delivered Imagery BA intervention on behavioral activation and depressive symptoms in individuals with depression. The imagery BA intervention will be compared to a wait-list control group.

While there are promising pre-clinical studies testing the impact of the imagery-enhanced activity scheduling procedure on motivation and reward anticipation (Heise et al., 2022; Renner et al., 2019) and one pilot randomized controlled trial testing the effects of an imagery BA intervention in a sample of patients with late life depression (Pellas et al., 2022), the present study will be the first to test an imagery BA intervention in an online setting with an adequately powered sample of individuals with depression.

This study includes at least two innovative aspects: First, the intervention that is tested in this study combines two evidenced-based therapeutic procedures (BA activity scheduling and mental imagery) into a new intervention. Although BA activity scheduling is an effective intervention in itself, not all patients with depression benefit from activity scheduling and symptoms of depression, such as a lack of energy and loss of pleasure from activities, might be barriers to successful application of activity scheduling. The mental imagery component might offer an opportunity to overcome these barriers by providing a “pre-experience” of the positive aspects of planned activities in the here-and-now while they are planned in. As several studies have shown that BA can be successfully implemented in an online format (for meta-analyses, see Alber et al., 2023; Huguet et al., 2018; recent studies involving online BA include Mueller-Weinitschke et al., 2023; Potsch & Rief, 2024), it will be interesting to see if the same is true for this novel intervention. If confirmed, this would potentially enable broad dissemination to reach individuals with depression who do not have access to other therapy resources or who are on waiting lists for treatment. Also in a face-to-face context, the imagery BA intervention is relatively straightforward to learn and does not require a high degree of training which would potentially foster further dissemination.

The second innovative aspect of the present study is the concurrent measurement of outcome (depressive symptom severity) and the putative mechanism underlying potential changes in this outcome, that is, behavioral activation. In a study testing an internet-delivered BA intervention in a sample of clinically depressed individuals, Fu et al. (2021) found that improvements in symptom severity were mediated and preceded by increases in activation levels. The present study should provide further insights into whether a similar pattern emerges if BA is augmented with mental imagery.

We expect that the imagery BA intervention is not associated with any risks or adverse effects. Previous studies in non-clinical (Heise et al., 2022; Renner et al., 2019) and clinical samples (Pellas et al., 2022, 2023) suggest that the intervention can be delivered in a safe way and is well accepted and tolerated.

One aspect that needs to be considered when interpreting the results of this study is the fact that we plan to compare the intervention to a wait-list control group. Due to the nature of the control condition, we will not be able to test the added effects of the new mental imagery component on top of the effects of BA activity scheduling alone. However, given that this is the first adequately powered trial in this context, starting with a wait-list control condition seems appropriate. Subsequent research should test the added effect of mental imagery simulation in activity scheduling by comparing an imagery-enhanced activity scheduling intervention to a standard BA activity scheduling intervention. Results of pre-clinical work already suggest that the imagery component does have an added value on motivation and reward anticipation for planned activities (Renner et al., 2019) specifically when the imagery component focusses on pre-experiencing pleasant aspects of planned activities (Heise et al., 2022). The added value of the mental imagery component on depressive symptom severity in patients with depression should be tested in subsequent studies.

In conclusion, although a number of evidence-based treatments for depression exist, including behavioral activation treatment, about half of the patients with depression do not get better in treatment and there is room for treatment innovation and improvement (Cuijpers et al., 2021). It is therefore important to explore new procedures to deliver and to amplify established evidenced-based interventions, such as BA activity scheduling. The imagery BA intervention that is tested in the present study is an example of this approach. The results of this study will provide the first empirical evidence of an imagery-enhanced BA intervention in an online setting for individuals with depression.

## Data Availability

Upon completion of recruitment and data analysis, the data of the presented study will be made available via the Open Science Framework. Alternatively, data will be made available by the authors on reasonable request.

## Appendix: List of Life Areas

- Relationships (family / friends / romantic)
- Sports & outside activities
- Hobbies / creativity / activities alone
- Self-care / recreation / spirituality
- Education & profession
- Everyday tasks
